## Abstract

**Background:**

Time-restricted eating (TRE) manages weight effectively, but choosing how long and what time window remain debatable. Although an 8:00 a.m. to 16:00 p.m. time frame is reported to show positive results in most weight loss trial, its safety and efficacy in overweight and obese women with polycystic ovary syndrome (PCOS) is uncertain. This randomized controlled trial is conducted to evaluate the safety and efficacy of TRE in specific populations.

**Objective:**

This study aims to assess the 6-month effects of TRE on weight change, metabolic improvement, reproductive recovery, and health-related quality of life in overweight and obese women with polycystic ovary syndrome (PCOS), compared to those who did not receive TRE.

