Although TRE has shown good effects such as diabetes, metabolic syndrome, and cardiovascular diseases [32,33], there are limited studies on it in overweight and obese women with PCOS. TRE has shown certain weight loss effects in anovulatory PCOS women [34]. However, due to the small sample size (n = 25), neglecting the impact on ovulation and the non-randomized design, the reliability of the conclusion remains to be verified.

Significant effects of TRE become apparent after 4 weeks of continuous implementation, with the potential for greater weight loss over an extended intervention period of 12 weeks [35,36]. To thoroughly investigate TRE’s impact on this specific demographic, a 12-week randomized controlled trial will be carefully planned. In the trial design, we will combine international health guidelines with the dietary habits of Chinese individuals, ultimately selecting 8:00 a.m. to 16:00 p.m. as the optimal feeding window [37,38]. In addition, to ensure the validity of the trial, calorie intake will be appropriately restricted. Following the conclusion of the trial, a 3-month follow-up will be conducted to further evaluate the long-term effects and safety of TRE. Through such an approach, we aim to comprehensively and precisely evaluate TRE’s efficacy in this population, offering effective, practical, and scientific dietary management strategies to these women, thus helping them achieve positive metabolic health.

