## Methods

### Study design and ethics

This prospective randomized controlled study will be used to evaluate the effects of TRE in overweight and obese women with PCOS. After signing the informed consent form, participants will be randomly divided into two groups for a 1-week baseline survey, a 12-week intervention, and a 6-month follow-up. Recruitment for the study began on July 20, 2024, and will end by June 20, 2025. Participants will provide written informed consent. This study was conducted in accordance with the Declaration of Helsinki, and approved by the Medical Ethics Committee of the University of South China (Number: NHHL027), and registered in the Chinese Clinical Trial Registry (ChiCTR 2400086815). If protocol changes are required, the study leader will communicate with ethics Committee members and trial registry staff.

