#### Support and follow-up

To ensure the effective implementation of the intervention and the accuracy of the data, we provided full support and close follow-up for all participants. First, all participants will receive personalized dietary counseling provided by a professional nutritionist. These consultations cover not only the development of meal plans, but also specific guidance on how to carry out these plans in real life. Participants will receive a detailed diet information booklet at the hospital with precise portion size recommendations, sample menus, and practical tips on how to properly schedule meals within a specific time window. In addition, we asked participants to keep a detailed food diary and to take photographs before and after each meal. This practice was designed to help participants better monitor their eating habits, while also providing us with an accurate source of data to assess when they ate and how much food they consumed.

In terms of follow-up, we have developed a strict monitoring plan. During the intervention, two researchers will contact the participants weekly by phone, not only focusing on their diet implementation, but also asking in detail and recording any possible adverse events (such as hunger pangs, dizziness, mood swings, etc.). For any questions or confusion encountered, the researchers will provide timely answers and necessary guidance to ensure participants’ compliance and the smooth conduct of the study. At the same time, participants’ food diaries and food photos will be regularly reviewed, using Chinese food composition lists to accurately assess their nutrient intake [41]. This step is essential to verify the implementation of the diet plan and adjust the diet regimen.

Our follow-up did not stop after the intervention. Instead, we will continue to contact participants by phone on a monthly basis to check on their weight changes and encourage them to share any new developments regarding their diet, lifestyle habits, or health status. This long-term follow-up mechanism will help us evaluate the long-term effects of time-restricted dietary interventions and provide valuable data to support future studies. Fig 1 shows the schedule for enrolment, intervention and assessment as required by SPIRIT.

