### Measures

Study results will be measured at multiple time points and changes from baseline to each time point will be assessed. The results included objective indicators such as weight, sex hormones, metabolism, and subjective indicators such as quality of life [42], sleep quality [43], and psychological status [44]. We will not interfere with the normal treatment of PCOS women throughout the trial period. Table 1 summarized the details of the collection of outcome indicators.

**Table 1 pone.0316333.t001:** Outcome measures and measurement methods.

Outcome Measure		Collection Method/Tool			Details	Measurement Time Points
Weight and BMI		Multi-frequency bioelectrical impedance analyzer IOI scanner			Each participant will be asked to take the measurements after fasting (or three hours after eating and drinking) and after emptying their bladder and bowels. Each participant will be asked to take the measurement on an empty stomach (or three hours after eating or drinking water) and after defecating. Participants will take off their shoes and socks during the measurement, and their weight and height will be measured by the multi-frequency bioelectrical impedance analyzer IOI (IOI, Seoul, Korea) scanner to calculate their BMI (weight kg/ height m squared, kg/m^2^).	Intervention: baseline, once a week Follou-up: once a month
Sex hormones		Chemiluminescence immunoassay analysis			Participants will have their sex hormones measured between the 2nd and 4th days of their menstrual cycle; for those with amenorrhea, the date is not restricted. They will fast for 12 hours before the test. The tests will be conducted using chemiluminescence immunoassay analysis.	Baseline, 4^th^ week, 8^th^ week, 12^th^ week
Metabolic parameters		Fasting blood tests			Fasting blood tests will be conducted to analyze glucose metabolism parameters (glucose, insulin, HOMA-IR, and HbA1c levels) and lipid profile (triglycerides, total cholesterol, and LDL/HDL cholesterol).	
Body composition		Multi-frequency bioelectrical impedance analyzer IOI scanner			The measurement requirements are the same as the anthropometry, the body composition will be assessed by the IOI scanner, including body fat (kg), muscle (kg), water (L), inorganic salts (kg), protein (kg).	
**Outcome Measure**	**Collection Method/Tool**			**Details**		**Measurement Time Points**

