## Discussion

There is extensive literature suggesting that being overweight and obese can exacerbate symptoms and complications in women with PCOS [45,46]. Weight loss of 5% to 10% is sufficient to improve clinical symptoms such as menstrual disorders and insulin resistance [2]. Given the increased prevalence and severe consequences of overweight and obesity in PCOS, traditional dietary weight loss strategies suffer significant limitations. As TRE is an emerging strategy that can compensate for the shortcomings of traditional dietary interventions and can treat obesity and improve adult metabolism, we will conduct a randomized controlled trial to evaluate the safety and effectiveness of TRE interventions in overweight and obese women with PCOS.

There are strengths of the study protocol. Firstly, we will improve our study protocol and develop a more rigorous randomization, control design and more scientific sample sizes. Our study will adopt a randomized controlled study design, which can effectively prevent selection bias and improve the comparability between groups to ensure the objectivity and accuracy of research results. In the selection of sample size, we will choose a more appropriate calculation formula in order to get more scientific and effective results. Secondly, in terms of outcome measurement, specific indexes of overweight or obese PCOS will be selected to explore the effects of this dietary pattern on metabolic characteristics and even reproductive health. Data will be collected from the same individual at three different time points, which can eliminate inter-individual variance in the results. Thirdly, we combined evidence-based strategy and Chinese eating habits to choose the best eating window, which can improve the compliance of the trial and obtain significant results as well.

However, there are some limitations to our study. First, repeated questionnaires during the trial may induce bias. To avoid memory overlap due to insufficient time intervals, each questionnaire measurement interval will span six weeks, and all participants will complete offline surveys with uniform guidance provided by researchers. Second, this study does not guarantee blindness for study participants, thus introducing potential uncertainty. Nevertheless, we aim to mitigate this through blinded outcome assessors and data analysts.

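### The objective promises 6-month effects in four domains, but only weight/BMI is scheduled after week 12, and the follow-up length is given as both 3 and 6 months

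*Protocol article*

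**What the plan says.** The Objective in the Abstract sets the horizon: "This study aims to assess the 6-month effects of TRE on weight change, metabolic improvement, reproductive recovery, and health-related quality of life", each compared with women not receiving time-restricted eating.

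Study design and ethics gives the structure as "a 1-week baseline survey, a 12-week intervention, and a 6-month follow-up". The Abstract's Methods paragraph also has a 6-month follow-up. The Introduction, after describing the same 12-week trial, says: "Following the conclusion of the trial, a 3-month follow-up will be conducted to further evaluate the long-term effects and safety of TRE".

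Table 1 (Measures) schedules weight and BMI weekly during the intervention and monthly in follow-up. For sex hormones, and again for the questionnaire block, the entry is "Baseline, 4^th^ week, 8^th^ week, 12^th^ week". In the extracted text the time-point cells for metabolic parameters, body composition, SF-36 and HADS are blank beneath those entries. Compliance is scheduled monthly in follow-up, and adverse events are collected until the participant's last assessment.

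Support and follow-up describes the period after the intervention: "we will continue to contact participants by phone on a monthly basis to check on their weight changes". The Discussion says "Data will be collected from the same individual at three different time points" and, as a measure against memory overlap, that "each questionnaire measurement interval will span six weeks".

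**The concern.** The horizon in the objective matches neither the intervention period nor, for most domains, the measurement schedule. Three readings of the main time point are open: week 12, about month 6 and about month 9. They are different quantities. Week 12 is the effect while the eating window is in force. Month 6 is what persists about three months after it ends, and month 9 what persists about six months after.

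With weekly and then monthly weights, the text as it stands would allow the headline time point to be chosen after the results are seen. For the metabolic, reproductive and quality-of-life domains the problem is more basic: no measurement is scheduled at the horizon that the objective names.

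**Working it through.** **Inputs.** Objective horizon: 6 months (Abstract, Objective). Baseline survey: 1 week; intervention: 12 weeks (Study design and ethics). Follow-up: 3 months (Introduction) or 6 months (Abstract, Methods; Study design and ethics). Measurement times: Table 1. One month is taken as 30.4375 days.

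**The plan's own sample size, and whether it settles the time point.** N per group = 2 × (1.96 + 0.84)² × 3.87² / 2.5² = 37.57, rounded up to 38. With 20% dropout, 38 / 0.80 = 47.5, rounded up to 48, which matches the stated 48. The 2.5 kg difference carries no time point, so it does not say which horizon is meant. Nothing in this point changes the sample size.

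**Study end under each follow-up length.**
- Intervention: 12 × 7 / 30.4375 = 2.76 months.
- With 3 months of follow-up: 2.76 + 3 = 5.76 months from start of intervention. Adding the baseline week, 13 × 7 / 30.4375 + 3 = 5.99.
- With 6 months of follow-up: 2.76 + 6 = 8.76 months; with the baseline week, 8.99.

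Counted from the start, only the 3-month version ends at about month 6. Under the 6-month version the study runs to about month 9. The objective could then mean six months after the intervention, but the text does not say so.

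**Gap between last measurement and horizon.** Six months is 6 × 30.4375 / 7 = 26.1 weeks. The last scheduled hormone and questionnaire assessment is week 12, so the gap is 26.1 − 12 = 14.1 weeks. If the horizon is about month 9, the gap is longer.

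**Domains in the objective against Table 1.**
- Weight change: weekly to week 12, then monthly. Covered.
- Reproductive recovery (sex hormones): weeks 0, 4, 8 and 12, stated outright. Not covered after week 12.
- Metabolic improvement: blank cell below the sex-hormone row. Read as merged, weeks 0, 4, 8 and 12. Not covered after week 12.
- Quality of life (SF-36): blank cell below the sleep-quality row in the questionnaire block. Read as merged, the same weeks. Not covered after week 12.

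Three of the four domains therefore have no scheduled measurement after week 12. Multiple imputation, which Data analysis names as an option for missing data, does not help: it fills in values missed at a planned visit and cannot recover a treatment difference at an occasion when neither arm is measured.

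**Discussion against Table 1.** Six-week spacing over 12 weeks gives weeks 0, 6 and 12, which is three occasions. Table 1 gives weeks 0, 4, 8 and 12: four occasions, four weeks apart.

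**The case against.** The best defence is that the week-12 stop is partly inferred. Only the sex-hormone and sleep-quality rows print their time points. Metabolic parameters, body composition, SF-36 and HADS depend on reading blank cells as merged, Fig 1 (the assessment schedule) is not shown, and the Abstract says secondary outcomes are evaluated every month without giving an end. This stands as a caveat. Against it, Table 1 states monthly follow-up where it intends it, for weight/BMI and compliance, and the follow-up described in the text is a telephone call with no blood test or questionnaire. For sex hormones no inference is needed. Fig 1 could not remove the conflict over follow-up length, which lies in the text.

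Four stronger readings are tempting, and the documents do not support them:
- A reader might infer that nothing but weight/BMI is collected after week 12. Compliance is scheduled monthly in follow-up and safety runs to the last assessment, so the gap concerns the efficacy domains only.
- A reader might infer that follow-up weight is self-reported by phone. The text does not say that the calls replace the scanner. The Control group section describes similar calls during the intervention, when Table 1 has weekly scanner weights. This is an ambiguity to settle and not a shown conflict.
- A reader might take the Discussion's three time points as a plain contradiction. They could be the three post-baseline occasions at weeks 4, 8 and 12.
- A reader might conclude that the protection against memory overlap is absent. The questionnaires are still spaced, by four weeks, and are completed offline with uniform guidance. Only the stated six-week interval is wrong against Table 1.

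It can also be said that the Abstract's Methods and Study design and ethics agree on 6 months, which leaves the Introduction as the outlier. That may show which text is older, but it does not repair the objective.

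**Conclusion.** The point holds. A 6-month between-group effect cannot be estimated for three of the four domains in the objective, because their last scheduled measurement is at week 12, about 14 weeks before month 6. This is certain for sex hormones as printed. For metabolic parameters and SF-36 it assumes merged cells in Table 1 and a Fig 1 that agrees with the table. Separately, and with no such assumption, the follow-up length differs by 3 months between sections, which puts the end of the study near month 6 or near month 9.

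This should be corrected before analysis, because it decides what the trial can claim. The sample size is unaffected, and the 12-week comparison is fully supported by the schedule. The Discussion's questionnaire interval and the source of the follow-up weight are minor.

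**What to change.** - Restate the objective as the 12-week effect, with week 12 as the time point for all efficacy domains.
- State one follow-up length in the Abstract, Introduction and Study design and ethics. Which one is the investigators' decision.
- Limit long-term claims to weight/BMI plus safety and compliance. Safety must stay, since the Introduction names it as a purpose of follow-up.
- Print the time points in every row of Table 1 and check them against Fig 1.
- Minor: change the Discussion's six-week interval to Table 1's four weeks, and say whether baseline counts among the occasions.
- Minor: confirm that the follow-up weight used in analysis is the scanner value in Table 1 and not a phone report.

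The cost is wording, the notice to the ethics committee and registry that the protocol already foresees for changes, and a narrower long-term claim. If the investigators want 6-month effects in all four domains, the alternative is to schedule blood tests and questionnaires at that horizon in both groups. That costs an added assessment per participant.

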**Methods:**

This randomized controlled trial will enroll 96 overweight and obese women with polycystic ovary syndrome (PCOS), who will be randomly assigned to either a TRE group (with an eating window from 8:00 a.m. to 16:00 p.m.) or a control group (without eating time restrictions), with 49 participants in each group. Evaluators and data analysts will remain blinded to group allocation throughout the study. The primary outcomes, including changes in weight and body mass index (BMI), will be assessed weekly. Secondary outcomes, encompassing alterations in sex hormones, metabolic parameters, body composition, sleep quality, quality of life, anxiety, and depression, will be evaluated monthly. Compliance and safety will be continuously monitored throughout the study. Additionally, a 6-month follow-up will be conducted at the end of the trial to assess the long-term effects of TRE. Statistical analysis will include the Anderson-Darling test for normality, T-test/Wilcoxon test based on distribution, mixed-effects models for assessing time/group effects, Cox model for time-to-event analysis, repeated ANOVA for change analysis, and sensitivity analysis. All tests will be conducted using appropriate software, with a significance level set at P<0.05. Missing data will be imputed.

**Discussion:**

The purpose of this study protocol is to further evaluate the effects of TRE in overweight and obese women with PCOS through a randomized controlled trial (RCT). Findings from this study are expected to provide new dietary intervention strategies for overweight and obese PCOS participants.

**Ethics and dissemination:**

This study has received ethics approval from the Medical Ethics Committee of the University of South China (Number: NHHL027). Participants are included after signing informed consent. Results will be submitted for publication in peer-reviewed journals.

**Trail registration:**

**Trail registration number:**
ChiCTR2400086815.

## Introduction

Polycystic ovary syndrome (PCOS) is a common gynecological endocrine disorder with an incidence rate of 5%-18% [1–3]. Globally, approximately 60% of PCOS women are accompanied by overweight or obesity [4]. Previous studies have shown that overweight and obesity are significant risk factors for women with PCOS [5,6]. Overweight and obese women with PCOS amplify conception challenges and lower assisted reproductive technology success rates, while also heightening risks of cardiovascular disease, diabetes, and mental health issues like anxiety and depression [7–10]. Consequently, weight loss is vital for PCOS women to restore fertility, prevent chronic diseases, and enhance their overall well-being [11]. Among weight reduction strategies, dietary intervention stands out as a key management approach [12]. Numerous dietary interventions for PCOS treatment have been suggested, including low-calorie [13], low-carbohydrate [14], low-glycemic index [15], Mediterranean [16], and ketogenic diets [17]. However, these methods face challenges, including adherence, metabolic adaptation, and psychological strain [18]. Time-restricted eating (TRE), an emerging eating pattern, focus on limiting daily eating to specific periods, while completely avoiding calorie-containing intakes during the rest of the day [19]. TRE effectively reduces body weight, lowers blood sugar levels, and improves insulin sensitivity and metabolism by controlling the duration and timing of food intake [20]. Different durations and windows of food intake yield varying effects. 4-hour and 6-hour eating windows reduced patients’ weight and improved cardiometabolic health, but adverse effects such as nausea, headaches, and constipation are reported [21,22]. 10-hour and 12-hour eating windows did not significantly affect weight loss or insulin sensitivity improvement [23–25]. The 8-hour TRE window is most extensive, but results vary based on the specific eating window. Neither too early nor too late time window can achieve the desired effect, or even have a negative impact [26–28]. At present, the time window of 8:00–16:00 works best, which, according to some studies, is consistent with the human body’s circadian rhythm [29–31].

Although TRE has shown good effects such as diabetes, metabolic syndrome, and cardiovascular diseases [32,33], there are limited studies on it in overweight and obese women with PCOS. TRE has shown certain weight loss effects in anovulatory PCOS women [34]. However, due to the small sample size (n = 25), neglecting the impact on ovulation and the non-randomized design, the reliability of the conclusion remains to be verified.

Significant effects of TRE become apparent after 4 weeks of continuous implementation, with the potential for greater weight loss over an extended intervention period of 12 weeks [35,36]. To thoroughly investigate TRE’s impact on this specific demographic, a 12-week randomized controlled trial will be carefully planned. In the trial design, we will combine international health guidelines with the dietary habits of Chinese individuals, ultimately selecting 8:00 a.m. to 16:00 p.m. as the optimal feeding window [37,38]. In addition, to ensure the validity of the trial, calorie intake will be appropriately restricted. Following the conclusion of the trial, a 3-month follow-up will be conducted to further evaluate the long-term effects and safety of TRE. Through such an approach, we aim to comprehensively and precisely evaluate TRE’s efficacy in this population, offering effective, practical, and scientific dietary management strategies to these women, thus helping them achieve positive metabolic health.

